## Discussion

To our knowledge, this study is the first to assess the long-term noncancer health outcomes of early surgical menopause in women with a high familial risk of ovarian cancer, focusing on CVD, bone health, cognition, and HRQoL. The issue is important as RRSO at the age of 35-45 years is an increasingly common procedure in *BRCA1/2* mutation carriers, with an estimated uptake in the Netherlands of 81% to 99% [4,5]. We have designed a nationwide, multicenter, multidisciplinary, cross-sectional study with prospective follow-up, comparing 500 women who have undergone RRSO before 45 years of age (more than 10 years of follow-up) with 250 women who have undergone RRSO after 55 years of age or who have not undergone RRSO. The unique features of our study are near complete information on the occurrence of RRSO in the cohort and long-term follow-up of all cohort members, allowing the selection of the eligible population for this study at least 10 years after RRSO. Our study is nested in a cohort of women with a high familial risk of breast and ovarian cancer, which will allow us to evaluate potential differences in disease risks between our study population and the entire cohort in order to quantify any survivorship and selection bias and to adequately interpret the magnitude of our effect sizes.

At present, it is still unclear whether early surgical menopause can be considered as a clinically relevant risk factor for CVD. During normal menopausal transition, CVD risk increases [23,26,78,80]. Women with an early natural menopause (<40 years) are at higher risk of developing CVD, and they have a higher CVD mortality than age-matched peers [23-26]. However, it has been debated whether this association is causal, and it has been speculated that this might also be explained by early vascular aging predisposing to both POI and cardiovascular disease [30,81]. If this is true, an artificial early menopause might not be associated with increased CVD risk. In support of this, a recent study by Krul et al showed that cancer treatment–induced POI did not affect CVD risk [82]. This renders it even more interesting to investigate CVD risk in women with surgically induced early menopause. To date, this has been addressed in only a few studies, with inconsistent results and with a median follow-up of at the most 5 years, which is too short considering potential delayed effects of estrogen deprivation and the long life expectancy of these women. Furthermore, previous studies vary with respect to HRT use and age at surgery [27-29].

The association between early surgical menopause and long-term bone health has also been rarely examined. Studies were inconclusive regarding decreased BMD and increased fracture risk, and whether these risks remain increased over time [83,84]. In addition, the effect of early RRSO on cognition has not yet been examined. However, both unilateral and bilateral oophorectomies at later ages have been associated with cognitive impairment and dementia, suggesting neuroprotective effects of estrogen on the brain. These effects appear to be age dependent [34,85].

After menopause, women more often report sexual and urogenital problems, such as urinary incontinence, recurrent urinary tract infections, impaired libido, and dyspareunia, which interfere with HRQoL. Women with POI experience these problems even more [86,87]. We do not know if these results can be generalized to surgical early menopause. Studies on long-term HRQoL after RRSO are limited and highly biased by HRT use.

One of the major strengths of our study is that it will be the first to examine the health effects of premenopausal RRSO at less than 45 years with a follow-up of over 10 years compared to controls with natural menopause. Additionally, owing to the large number of participants, we will have sufficient power for subgroup analyses. A limitation of our study could be survivor bias. Owing to the inclusion criterion of at least 10 years of follow-up, patients may already have died of relevant study outcomes before study inclusion. However, as we conduct the cross-sectional study within a well-characterized cohort, we can assess the extent of such bias by collecting cause of death information for potentially eligible but already deceased women.

This initial cross-sectional study will provide prevalence rates of noncancer outcomes. Therefore, we will follow the study cohort prospectively to obtain incidence rates of outcomes of interest and evaluate changes in outcomes over time.

To summarize, the current literature lacks information on long-term noncancer outcomes in women at increased risk of breast/ovarian cancer who have undergone early oophorectomy. With this study, we will be able to provide insights into the prevalence and severity of CVD, osteoporosis, cognitive impairment, and HRQoL effects after RRSO. This knowledge will yield evidence-based information for women and for health care providers about the long-term effects of early RRSO. The results can be incorporated in decision-support tools about risk-reducing surgeries in *BRCA1/2* mutation carriers considering RRSO and can be used to offer individualized counseling about additional screening and interventions for noncancer diseases or complaints after RRSO.

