### Recruitment

We will include 500 women who have undergone RRSO before the age of 45 years, with a follow-up period of at least 10 years (the early RRSO group). We will compare them with 250 women from the same cohort (frequency matched on current age) who have not undergone preventive RRSO or have undergone RRSO at the age of 55 years or above (the late/non-RRSO group). The exclusion criteria are a metastatic disease; a serious physical comorbidity or psychiatric disorder; a language barrier; a metal cardiac valve; a bare metal coronary stent, since the reflection of the stent would interfere with the computed tomography scan; and natural POI before the age of 40 years. A history of nonovarian cancer, including breast cancer, is not a reason to be excluded.

Eligible women who are alive will be invited for a clinic visit and questionnaire survey that will assess CVD status, BMD, cognitive functioning, and HRQoL. For eligible women who have died, we will collect information on the causes of death to examine selection bias.

Participants will be selected from the dynamic nationwide HEBON study cohort, a national collaboration on HEreditary Breast and Ovarian cancer in the Netherlands, with women tested for *BRCA1/2* germline mutations included since 1997 by all eight Dutch University Medical Centers (UMCs) and the Netherlands Cancer Institute (NKI). The cohort currently consists of over 3600 proven female *BRCA1/*2 germline mutation carriers. Participants have given informed consent for linkage with the Netherlands Cancer Registry and the Dutch Nationwide Pathology Database (PALGA), which can provide information on all prophylactic mastectomies and salpingo-oophorectomies performed in the Netherlands since 1991. This provides us with nearly complete information on the occurrence of RRSO. Data on lifestyle, family history, reproductive factors, and hormone use have been collected from HEBON participants through questionnaires [44].

Figure 2 provides a schematic overview of the patient selection and eligibility criteria of our study population.

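### The stated comparison of the study population with the entire cohort cannot quantify selection bias in the early versus late/non-RRSO contrast; the reference should be eligible non-participants within each RRSO group

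*Protocol article*

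**What the plan says.** The Discussion states both the comparison and its purpose. The team can "evaluate potential differences in disease risks between our study population and the entire cohort in order to quantify any survivorship and selection bias". The comparator is the whole cohort, and no split by RRSO group is mentioned. The same sentence then names the use to be made of the result: "and to adequately interpret the magnitude of our effect sizes".

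Recruitment adds a second check: "For eligible women who have died, we will collect information on the causes of death to examine selection bias". The Discussion returns to it as the answer to survivor bias: "we can assess the extent of such bias by collecting cause of death information for potentially eligible but already deceased women".

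For the living, Recruitment says only this: "Eligible women who are alive will be invited for a clinic visit and questionnaire survey". It describes no comparison with those who decline.

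On the source population, Recruitment says: "The cohort currently consists of over 3600 proven female" BRCA1/2 carriers. It also says what is held on cohort members: "Data on lifestyle, family history, reproductive factors, and hormone use have been collected from HEBON participants through questionnaires", together with linkage to the national cancer registry and the pathology database.

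**The concern.** The comparator and the purpose do not fit each other, for two reasons.

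First, the study sample is narrowed by design and the cohort is not. A difference in disease risk between them can come from eligibility and the sampling ratio alone.

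Second, the effect sizes to be interpreted are contrasts between two RRSO groups. Selection biases an odds ratio to the extent that outcome-related participation differs between those groups. A comparison of the whole sample with the whole cohort does not show that difference.

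At stake is how the main results are read. Women in one group with complaints may be keener to attend, and women in the other may be more reluctant to come for a CT and DXA visit. That could create or hide an association while the stated check gives reassurance. The check could equally raise an alarm that says nothing about the contrast. According to the article, the results are meant for follow-up guidelines and decision-support tools.

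**Working it through.** **1. Who is compared with whom.**

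| | Study sample | Entire cohort |
|---|---|---|
| RRSO status | early: "500 women who have undergone RRSO before the age of 45 years, with a follow-up period of at least 10 years"; otherwise none, or at 55 or above | no such limit stated |
| Current age | 55 or above (Recruitment), frequency matched | no such limit stated |
| Health | metastatic disease and serious comorbidity excluded | no such limit stated |
| Group ratio | 500:250, fixed by design | whatever the cohort contains |

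**2. Inputs.** The bias check carries no figure of its own. For scale I take the planning values in Sample Size Calculation: 10% prevalence in the late/non-RRSO group, an odds ratio (OR) of 1.9, and 500 versus 250 women.

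- OR 1.9 on 10%: odds 1.9 × 0.10/0.90 = 0.211, so early-group prevalence is 0.211/1.211 = 17.43%.
- A two-proportion calculation with these values gives 78.6% power against the stated 80%. That figure is not in dispute.
- Overall prevalence at 2:1: (2 × 17.43 + 10)/3 = 14.95%.

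The documents give no participation rates, so every *k* below is an assumption. The outcome stands for any disease of about this prevalence.

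**3. Formula.** Let *k* be the participation rate of women with the outcome divided by that of women without it, in one group. The observed odds in that group are the true odds × *k*. Hence

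observed OR = true OR × (k_early / k_late).

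**4. No overall difference, contrast biased.**

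- True OR 1.0, 10% in both groups, k_early 1.15, k_late 0.713. Observed prevalences are 11.33% and 7.34%; overall (2 × 11.33 + 7.34)/3 = 10.0%, unchanged. Observed OR = 1.15/0.713 = 1.61.
- True OR 1.9, k_early 0.85, k_late 1.518. Observed prevalences are 15.21% and 14.43%; overall 14.95%, unchanged. Observed OR = 1.9 × 0.85/1.518 = 1.06.
- Exact cancellation is not needed. True OR 1.0, k_early 1, k_late 0.75: the late group shows 0.075/0.975 = 7.7%; overall (2 × 10 + 7.7)/3 = 9.2% against 10.0%. The standard error at n = 750 is √(0.1 × 0.9/750), about 1.1 points, so this would not stand out. Observed OR = 1/0.75 = 1.33.

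**5. Overall difference, contrast unbiased.** True OR 1.9, *k* = 0.6 in both groups. Observed prevalences are 11.24% and 6.25%; overall 9.6% against 14.95%. That is a fall of 5.4 points with a standard error of about 1.3. The OR stays at 1.9.

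**6. No selection at all, but ineligible women in the reference.** Assume that 20% to 50% of the cohort is eligible, with the same 2:1 mix, and that prevalence among ineligible women is 2% to 5%.

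- Lowest: 0.2 × 14.95 + 0.8 × 2 = 4.6%.
- Highest: 0.5 × 14.95 + 0.5 × 5 = 10.0%.

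The sample shows 14.95% throughout, and the OR is unbiased. The fixed ratio can add a difference too. If eligible women in the cohort were split 1:1 (assumed), their overall prevalence would be (17.43 + 10)/2 = 13.7%.

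**7. What a within-group comparison gives.** For a disease recorded in participants and non-participants alike, comparing them within each RRSO group estimates k_early and k_late. Their ratio is the bias factor: 1.61 and 0.56 in the first two cases of step 4, and 1.0 in step 5.

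**The case against.** The strongest reply is that this is one Discussion sentence about what the cohort makes possible, not an analysis specification. A reader might infer that the plan fixes a crude, pooled comparison. The documents do not say so. They neither state nor exclude a split by RRSO group, age standardisation or restriction to eligible women, and the full protocol may provide them. That stands as far as the missing split is concerned. It does not rescue the comparator, because the entire cohort is named explicitly and is the wrong reference even after a split.

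A reader might also infer that eligible non-participants are ignored altogether. That is wrong: the cause-of-death check concerns eligible women who have died. The gap is living eligible women who decline.

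Nor is every overall difference a false alarm. The Discussion says the study will provide prevalence rates, so a shift in overall prevalence among eligible women, as in step 5, is genuine bias in a reported quantity, though not in the contrast. Milder shifts may not be detectable either. With *k* = 1.2 in both groups, 10% becomes 0.12/1.02 = 11.8%, only about 1.5 standard errors at n = 750.

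Finally, re-weighting is no cure. The documents list no CAC, BMD or cognition data for non-participants, so weights built on held variables cannot remove selection on those outcomes, except as far as the variables predict them. This stands, and it limits what the fix can promise.

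**Conclusion.** The point holds for the comparison as worded. Setting the study population against the entire cohort does not quantify selection bias in the early versus late/non-RRSO contrast, and should not be used to interpret its size. That both kinds of misreading are possible follows from the algebra. The sizes (a null OR observed as 1.33 or 1.61, an OR of 1.9 observed as 1.06) rest on assumed participation rates; they show what is possible, not what is likely. The documents do not support saying that the plan has no check on eligible non-participants, that it prescribes pooling, or that selection bias is present. This is a cheap improvement to a stated method. It is not an error in the primary analysis.

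**What to change.** In the Discussion, replace the entire cohort as the reference. Suggested text: *Participants will be compared with eligible non-participants (living women who decline or do not respond, and eligible women who have died), separately in the early RRSO and late/non-RRSO groups and standardised for age, on HEBON questionnaire data and cancer-registry and pathology linkage. Causes of death will be reported by RRSO group.*

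Contrasts weighted for participation may be added as a sensitivity analysis. The text should then say that they correct only for measured predictors of participation.

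The cost is modest extra analysis on data already held, plus a record of invitation and response by RRSO group. With 364 of 750 women enrolled at the time of the article, that record could still be kept for the rest of recruitment. Any weighted analysis will have wider intervals.

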## Appendix

Multimedia Appendix 1 Peer-review report by KWF.

## Abbreviations

ACS: Amsterdam cognition scan
AGEs: advanced glycation end products
AS: Agatston score
AU: Agatston units
BMD: bone mineral density
BRCA: breast cancer gene
BTM: bone turnover marker
CAC: coronary artery calcification
CVD: cardiovascular disease
DXA: dual-energy X-ray absorptiometry
HEBON: HEreditary Breast and Ovarian cancer in the Netherlands
HRQoL: health-related quality of life
HRT: hormone replacement therapy
NKI: Netherlands Cancer Institute
POI: premature ovarian insufficiency
PWV: pulse wave velocity
RRSO: risk-reducing salpingo-oophorectomy
UMC: University Medical Center
